### Recruitment of participants

Participants will be residents living in participating retirement villages, recruited with the help of RLOs and village managers. Residents will be recruited using a range of strategies, which include:

• distributing invitation forms to all residents in each village;

• displaying a poster on the notice board or in the common area of each village; and

• advertising the study in the villages' newsletters and/or on the villages' multi-screen televisions (where available).

Residents who are interested in the study will be asked to complete the invitation form and return it to the study investigators using a provided reply-paid envelope, or to contact the study investigators. The invitation form includes questions that ask for the resident's name and contact details, and assess their eligibility for participating in the study. Returned invitation forms will be used to identify and select residents who are eligible for the study. Eligible residents will be invited to participate in the study over telephone. Those who are interested in participating after this initial discussion will be sent a plain language statement, a consent form and a questionnaire. They will be asked to complete the consent form and questionnaire, and return them to the investigators. Once written consent is obtained, eligible residents will be enrolled in the trial and allocated to either PIG or UCG depending on the location of the retirement village they live in.

### Inclusion criteria

Residents who meet the following criteria will be eligible to participate in the study:

• living in one of the participating retirement villages;

• aged 55 years and above;

• using three or more prescribed medications;

• expecting to visit their GP in the next three months;

• expecting to be available for follow-up for at least six months from baseline; and

• available to attend an education session.

### Exclusion criteria

Residents will be ineligible to participate in the study if they have any of the following characteristics:

• received a HMR in the previous 12 months;

• planning to move from their current retirement village in the next six months;

• unable to give written informed consent; or

• unable to communicate in English.

The aim of the PHARMER trial is to target residents who have not received a HMR in the previous 12 months and improve their uptake of HMR using educational interventions. Those who have had a HMR experience in the previous 12 months are less likely to receive any additional benefits from the educational interventions because they are already aware of the benefits of HMR; and they are also less likely to receive another HMR referral from their GPs in the next 12 months, unless their condition changes (e.g. a recent hospitalisation) and requires more frequent review.

### Sample size

The sample size required for this study was calculated based on the HMR uptake in the previous 12 months (6%) reported in our recent survey [3]. From this figure, we anticipate the uptake of HMR in the UCG to be 6% after 12 months, 3% after 6 months and 1.5% after three months. To demonstrate that the intervention increases the uptake of HMRs from 3% (in the UCG) to 20% (in the PIG) at six months (considered to be a relatively conservative but clinically meaningful increase), with 80% power and a two-sided alpha value of 0.05, 55 participants will be required in each group (total of 110 participants). Allowing for 20% drop-out or loss to follow-up, and 20% for clustering effects, at least 77 participants will be recruited into each arm at baseline (total of at least 154 participants).

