### Identification and selection of retirement villages

Retirement villages eligible for the study, such as those with a representative officer (also known as Resident Liaison Officer [RLO]) from the Residents of Retirement Villages Victoria Inc. (RRVV) [10], will be identified in consultation with an officer of the RRVV. Eligible retirement villages meeting the study criteria will be identified by RRVV from their member database. Using the list provided by RRVV, a convenience sample of ten retirement villages will be selected for the study based on the following factors:

• having at least 100 units;

• having at least 20 residents who are members of RRVV; and

• geographical location (northeast and southwest regions).

The two geographical locations will be used to avoid potential contamination (see cluster randomisation). The geographical locations (northeast or southwest) will be randomised to intervention group (Pharmacist Intervention Group [PIG]) or control group (Usual Care Group [UCG]). Each group will include five retirement villages and will have at least 15 km between the PIG and UCG retirement villages. Selected villages should have at least 20 RRVV members to enhance recruitment of participants.

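### The 80% power treats the clustering allowance as known; with between-village variation estimated from ten villages (8 df), power for 3% vs 20% is about 70–75%

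*Protocol article*

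**What the plan says.** The Sample size section sets out to show that the intervention "increases the uptake of HMRs from 3% (in the UCG) to 20% (in the PIG) at six months", and gives the requirement as "with 80% power and a two-sided alpha value of 0.05, 55 participants will be required in each group". It then inflates: "Allowing for 20% drop-out or loss to follow-up, and 20% for clustering effects", which brings the minimum to 77 per arm (154 in total). No intracluster correlation (ICC) is given.

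Identification and selection of retirement villages fixes the number of clusters: "Each group will include five retirement villages and will have at least 15 km between the PIG and UCG retirement villages". Cluster randomisation says that two geographical regions are randomised, not the ten villages. Data analysis compares uptake between the groups with a chi-square test and mentions no adjustment for village.

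**The concern.** An allowance of "20% for clustering effects" is a variance inflation. It enlarges the standard error by a preset factor but leaves the reference distribution normal, with critical value 1.960. If the analysis estimates between-village variation from the data, ten villages in two arms leave 2 × 5 − 2 = 8 degrees of freedom, and the critical value is 2.306. With so few clusters, that difference costs several points of power, and the plan has no term for it.

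The stated power and the analysis should describe the same test. If the analysis respects the villages, the chance of missing the stated effect is about 25–30%, not 20%. If it does not, the nominal power is met but the 5% error rate is not assured.

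**Working it through.** **Inputs.** From Sample size: 3% vs 20%, two-sided alpha 0.05, 80% power, 20% loss, 20% for clustering (read as design effect 1.2), 77 enrolled per arm. From Identification and selection of retirement villages: five villages per arm. The ICC of 0.05 used in step 5 is an assumption, because the documents give none.

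**1. The plan's own figure.** Pooled normal formula, mean rate 0.115:

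n = [1.960 × √(2 × 0.115 × 0.885) + 0.842 × √(0.03 × 0.97 + 0.20 × 0.80)]² / 0.17² = (0.884 + 0.366)² / 0.0289 = 54.1, so 55 per group. This reproduces. Then 55 × 1.4 = 77, so the two allowances were added.

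**2. What 77 per arm delivers.**
- Analysed: 77 × 0.8 = 61.6 per arm, or 61.6 / 5 = 12.3 per village.
- ICC implied by a design effect of 1.2: 0.2 / (12.32 − 1) = 0.018. With the 15.4 enrolled per village it is 0.2 / 14.4 = 0.014.
- SE = √[1.2 × (0.0291 + 0.1600) / 61.6] = 0.0607.
- Noncentrality = 0.17 / 0.0607 = 2.80.

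**3. Power by reference distribution.**
- Normal, critical value 1.960: 80%.
- Noncentral t, 8 df, critical value 2.306: 69%.
- The approximate cost in sample size is [(2.306 + 0.889) / (1.960 + 0.842)]² = 1.30.

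**4. Simulation** (beta-binomial, 62 analysed per arm in villages of 12 or 13, ICC about 0.018, 100,000 or more runs):

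| Test | Power, 3% vs 20% | Type I error at common rates of 3%, 11.5%, 20% |
|---|---|---|
| Village t-test, raw proportions | 71% | 3.5%, 4.8%, 4.9% |
| Village t-test, empirical logit or arcsine | 75% | about 4.5–5.5% |
| Chi-square divided by a preset 1.2 | 83% | 2.3%, 4.9%, about 5.2% |
| Chi-square as planned | 88% | 5.2%, 7.2%, 7.0% |

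**5. Sensitivity.**
- Combining the allowances multiplicatively (55 × 1.2 / 0.8 = 82.5, so 83 per arm) moves the raw-proportion figure only from 69% to 72%. The shortfall therefore comes mainly from the degrees of freedom.
- With no clustering at all, the 8-df tests give about 77% (raw) and 80% (transformed).
- On raw proportions, 80% power needs an uptake of about 23.4% in the intervention arm.
- If the ICC were 0.05 (assumption), the design effect is 1 + 11.32 × 0.05 = 1.57. Raw-proportion power is then 58% by formula and 60% by simulation, and the transformed tests give 67%. The chi-square divided by a preset 1.2 then has a type I error of 8.5–9% at rates of 11.5–20%.

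**The case against.** A reader might infer that no analysis respecting the villages can reach 80%. That is too strong. Dividing the chi-square by the plan's own design effect gives 83% power at about nominal size, provided 1.2 is the true value. This is the analysis that the 20% allowance corresponds to. Its weakness is that it cannot learn from the data that 1.2 is wrong, as step 5 shows at an ICC of 0.05.

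A reader might also take 70% as the village-level figure. It belongs to the t-test on raw proportions, which suits 3% vs 20% poorly because the two variances differ about fivefold (0.160 against 0.029). Transformed scales recover about five points at the correct size.

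A third objection is that the planned test is a chi-square, for which 55 is right. That stands: the 55 is not an arithmetic error. It also changes the risk in the plan as written. With the chi-square the danger is an excess of false positives, not a missed effect. The low-power concern applies once the analysis respects the clustering that the sample size already budgets for.

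Finally, only two regions are randomised, so 8 df is not strictly the design's own figure. With one region per arm, village-level degrees of freedom do not separate intervention from region. This makes 80% harder to defend, but 70–75% must then be labelled as the favourable case. That an article gives no ICC is not held against it here; the point is the power figure it does state.

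**Conclusion.** The point holds in this form. The stated 80% relies on a normal reference and a design effect treated as known. When between-village variation is estimated from ten villages, power under the plan's own allowances is about 70% on raw proportions and about 75% on a logit or arcsine scale, a shortfall of roughly 5 to 10 points. The planned chi-square exceeds 80% only by ignoring the villages, with a type I error up to about 7%.

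These figures assume 20% loss, a design effect of 1.2 (ICC about 0.018), near-equal village sizes, and villages treated as the units although regions are randomised. A larger ICC lowers them. The number recruited need not change, but the power statement and the primary analysis should be brought into line.

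**What to change.** Keep 77 per arm. In Sample size, replace the 80% claim with text such as:

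> About 70–75% power for 3% vs 20% with a village-level analysis (five villages per arm, 8 df, 20% loss, design effect 1.2, implied ICC about 0.018), or 80% power for 3% vs about 23% on raw proportions; about 60–67% power for 3% vs 20% if the ICC were 0.05 (assumption). These figures treat villages as the units although two regions are randomised, so they are the favourable case.

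In Data analysis, replace the chi-square as the primary comparison of uptake with that village-level analysis and name its scale, so that the test and the stated power match. Changing Sample size alone would leave the protocol quoting power for a test it does not plan to run.

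The cost is a few sentences in two sections and a less favourable power figure. No participants or villages are added.

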**Methods/Design:**

This is a multicentre prospective cluster randomised controlled trial. Ten retirement villages in Victoria, Australia will be recruited for this trial. Retirement villages will be selected in consultation with the Residents of Retirement Villages Victoria Inc. (RRVV), based on geographical locations (e.g. northeast or southwest), size and other factors. Residents from selected villages will be recruited with the help of RRVV Resident Liaison Officers using a range of strategies. Randomisation will be by geographical location to minimise contamination. Participating villages and residents will be allocated to either Pharmacist Intervention Group (PIG) or Usual Care Group (UCG). Each group will include five retirement villages and will have at least 77 residents in total. The intervention (PHARMER) comprises educating residents regarding HMR, and using a risk assessment checklist by residents to notify their General Practitioners of their medication risk. Uptake of HMR and medication adherence will be assessed in both PIG and UCG at three and six months using telephone interviews and questionnaires.

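### The recruitment target of 77 per arm falls slightly short of the 55 per arm it is meant to protect: the stated drop-out and clustering allowances need 83, and 77 gives about 78% power on the protocol's own formula

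*Protocol article*

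**What the plan says.** The protocol article, under Sample size, sets the target difference as one that "increases the uptake of HMRs from 3% (in the UCG) to 20% (in the PIG) at six months". For that difference it states that "with 80% power and a two-sided alpha value of 0.05, 55 participants will be required in each group", 110 in total. It then inflates this number in one step: "Allowing for 20% drop-out or loss to follow-up, and 20% for clustering effects, at least 77 participants will be recruited" per arm, 154 in total. No inflation formula is shown. The Methods/Design part of the abstract carries the same figure, saying that each group "will have at least 77 residents in total". The abstract states no power.

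**The concern.** The two allowances act differently. Drop-out is a fraction of those recruited, so the number needed at follow-up is divided by the fraction retained. Clustering reduces the information per participant retained, so the number needed is multiplied by the design effect. The two therefore compound. Adding them and applying the sum to 55 gives too small a target.

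At stake is whether the stated minimum supports the stated power under the protocol's own assumptions. A reader would take 77 per arm as enough for 80% power after 20% loss and a 20% clustering penalty.

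**Working it through.** **Inputs**, all from the Sample size section: 3% and 20% uptake at six months; 80% power; two-sided alpha 0.05; equal arms; 20% drop-out; 20% for clustering; target 77 per arm. One assumption is added: the clustering allowance means a design effect of 1.2. The alternative reading is in step 5.

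**1. Reproduce the 55.** Pooled two-proportion formula without continuity correction, with p1 = 0.03, p2 = 0.20 and mean 0.115:

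n = [1.960 x sqrt(2 x 0.115 x 0.885) + 0.842 x sqrt(0.03 x 0.97 + 0.20 x 0.80)]² / 0.17² = 54.1, so 55 per arm.

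This matches the protocol. Power at 55 on this formula is 80.7%. Other versions do not match: continuity-corrected 66, unpooled 52, arcsine 47, one-sided 43.

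**2. Find the route to 77.**

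| Inflation | Result | Rounded up |
|---|---|---|
| 55 x (1 + 0.20 + 0.20) | 77.0 | 77 |
| 55 x 1.2 x 1.2 | 79.2 | 80 |
| 55 x 1.2 / 0.8 | 82.5 | 83 |
| 55 / 0.8 / 0.8 | 85.9 | 86 |
| 55 / 0.6 | 91.7 | 92 |

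Only the additive mark-up gives 77. Each of the other routes gives a larger number.

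**3. The target that the two allowances imply.** 55 x 1.2 / (1 - 0.20) = 82.5, so 83 per arm and 166 in total. The protocol has 77 and 154, a difference of 6 per arm and 12 in total.

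**4. What 77 delivers.** After 20% loss, 77 x 0.8 = 61.6 per arm remain. Dividing by the design effect, 61.6 / 1.2 = 51.3 effective participants per arm, below 55. On the formula of step 1:

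power = Phi{[0.17 x sqrt(51.3) - 1.960 x sqrt(2 x 0.115 x 0.885)] / sqrt(0.03 x 0.97 + 0.20 x 0.80)} = 77.9%.

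That is 2.1 points below 80% and 2.8 points below the 80.7% at 55. Put differently, 61.6 / 55 = 1.12, so after the stated loss, 77 leaves room for a 12% clustering allowance, not 20%. At 83 recruited, the effective number is 83 x 0.8 / 1.2 = 55.3 and power is 80.9%.

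**5. Alternative reading of the clustering allowance.** If 20% means that a fifth of the information is lost, the effective number is 77 x 0.8 x 0.8 = 49.3 and power is 76.1%. The matching target is 86 per arm (172 in total).

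**6. Sensitivity to the test.** Exact enumeration at 3% versus 20%:

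| n per arm | Pooled formula | Chi-square, uncorrected (exact) | Yates or Fisher (exact) |
|---|---|---|---|
| 51 | 77.6% | 82.1% | 69.9% |
| 55 | 80.7% | 85.3% | 74.8% |

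The level of power moves by several points in either direction with the choice of calculation. In each column, going from 55 to 51 costs about 3 to 5 points.

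**The case against.** The best case for leaving the text alone is that the effect is small and depends on the approximation. The Data analysis section names a chi-square test; without continuity correction its exact power at 51 per arm is about 82%, above the stated 80%. The unpooled normal formula gives 80.0% at 51.3. The target is also worded as a minimum, so recruiting a few more residents would close the gap. The additive step is deduced, not stated. Even the corrected number shifts with rounding: from the unrounded 54.1, 54.1 x 1.2 / 0.8 = 81.1, so 82 would do.

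Most of this stands as a limit on size, and it rules out saying that the trial is underpowered on every standard calculation. It does not rescue the arithmetic. The 55 comes from the pooled formula, and 77 does not carry that requirement through the two stated allowances. A corrected test would move power the other way, to about 70%. A minimum presented as sufficient should be sufficient on the basis used to derive it.

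A reader might infer something stronger: that the real shortfall is far larger, because ten villages leave only 8 degrees of freedom, or because the village intracluster correlation could be well above what a 20% allowance implies. The document does not support that as part of this point. The planned analysis is a chi-square test, not a village-level test, and allocation is by two geographical locations, so 8 degrees of freedom does not follow from it. The loss is also not caused by adding the allowances: replacing 1.960 by the t value on 8 degrees of freedom (2.306) in the same formula gives 65.8% at 77 per arm and still only 69.7% at 83. The article states no intracluster correlation, so any larger value would be the reviewer's own, and an article may leave that detail to the full protocol.

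**Conclusion.** The point holds, and it is minor. The stated 77 per arm does not follow from 55 per arm with 20% loss and a 20% clustering allowance, compounded in the usual way; 83 per arm (166 in total) does. At 77, power on the formula that reproduces 55 is about 78%, or about 76% if the clustering allowance is read as lost information.

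This rests on two things that the article does not spell out: that the allowances were summed, which is inferred from an exact match, and that 20% for clustering means a design effect of 1.2. The shortfall of about 2 points is specific to the pooled formula; the uncorrected chi-square test evaluated exactly still exceeds 80% at 51 per arm. The finding is therefore a misstated sample-size figure. It does not show that the trial is materially underpowered, and it does not settle whether a 20% clustering allowance is adequate for this design.

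**What to change.** Keep 77 per arm and restate the power in the Sample size section: about 78% on the protocol's formula, with 20% loss and a design effect of 1.2, noting that 83 per arm (166 in total) is the number that matches 80%. This changes one sentence and needs no extra residents; the cost is a slightly less favourable stated power. The abstract can then stay as it is, since it gives 77 without a power.

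If the sponsor prefers to keep the 80% claim, raise the target to 83 per arm and align the abstract. That means 6 more residents per arm, 12 in total.

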### Interventions in the Pharmacist Intervention Group (PIG)

At baseline, participants in the PIG will receive the intervention. The intervention to be tested includes several components:

a. HMR education session

• A pharmacist, who is accredited to undertake HMRs, will visit the PIG participants at their villages to deliver a group education session about the role of and benefits from HMR. Information leaflets about HMR will be given out to participants during these education sessions.

b. Medication risk assessment

• A medication risk assessment checklist will be adapted from a screening tool that was previously developed and published by the Pharmacy Guild of Australia (see Additional file 1: Pharmacy Guild of Australia's HMR consumer brochure). The HMR consumer brochure includes a self-administered checklist (with tick boxes) consisting of 16 items assessing a person's risk factors for medication-related problems (e.g. having recent hospitalisation, using multiple medicines, having recent changes to medication regimen, and using low therapeutic index medicines). The checklist will be completed by participants after the education session, with the pharmacist taking them through each question. The completed checklist will be used by the pharmacist to identify participants who have medication risk factors and thus could potentially benefit from a HMR.

c. New referral process for HMR

• Participants identified as having one or more medication risk factors will be referred to their GP. Referral will be made by asking the at-risk participant to give the completed medication risk checklist to their GP during their next GP visit and discuss the need for a HMR.

The group education session, including completion of the medication risk checklist, will take approximately one and a half hours.

### Routine care in the Usual Care Group (UCG)

Participants enrolled in the UCG will continue to receive routine care for six months during the study. No intervention will be offered to this group at any time during the study; however, they will not be denied a HMR if they are being offered this in the course of study as part of routine care. To ensure equity in both PIG and UCG and to avoid unfair disadvantage to any group, UCG participants will be offered a similar intervention to the PIG after the study period (e.g. at six months).

### Outcome measures and data collection

#### Outcome measures

The primary outcome measure will be participants' uptake of HMR; and secondary outcome measure will be participant self-reported medication adherence. HMR uptake will be assessed at three and six months from baseline, and medication adherence at six months.

#### Baseline data collection

The baseline characteristics of participants will be collected using a self-completed questionnaire. At baseline, the questionnaire will be sent to participants with the plain language statement and consent form. Information collected by the baseline questionnaire includes:

• demographics;

• medication use data, including medication management and problems experienced with medications;

• medication adherence [11];

• health-related quality of life [12]; and

• medication-related risk factors and eligibility for HMR (see Additional file 1: Pharmacy Guild of Australia's HMR consumer brochure).

Participants' medication adherence will be assessed using the self-reported Morisky scale [11]. The Morisky scale comprises four validated items, with responses to each item scored 0 for 'yes' and 1 for 'no' (except for the item 'Are you always careful in taking your medicines?' where the score is reversed). The total score on the Morisky scale ranges between 0 and 4; a score of less than 4 represents nonadherence.

Participants' health-related quality of life will be assessed using the self-reported Short Form (SF)-12^® ^Health Survey [12]. The SF-12^® ^Health Survey consists of 12 validated items relating to physical and mental health function. Responses to the items will be scored and computed using an online scoring program [13]. The scoring method will give two sets of results - Physical Component Summary (PCS) and Mental Component Summary (MCS) scores, with the scores ranging from 0 to 100, zero representing the lowest level of health and 100 representing the highest level of health [14].

Participants in both groups will be assessed for their medication-related risk factors and eligibility for receiving a HMR using the criteria or items in the Pharmacy Guild of Australia's HMR consumer brochure (see Additional file 1). Participants who fulfil one or more of these criteria will be considered eligible for a HMR.

Participants will be contacted by telephone to obtain incomplete or missing responses.

